### Ethical Considerations

This project did not meet the threshold for institutional review board (IRB) review and approval per Ochsner Health Systems (IRB) guidelines. Human participants were not consented for individual participation in this project. Patient data were stored behind a Health Insurance Portability and Accountability Act (HIPAA)–compliant hospital-wide internet firewall. All patient data are deidentified and anonymized before analysis and dissemination. Participants were not compensated for providing their data or for participation in this project. All staff involved in this protocol adhere to HIPAA. This QI initiative is purely a retrospective study of chart data or similar, and consent was not required for the procedures performed [23,27-31]. As such, it falls under the definition of nonhuman participants research according to both the US Department of Health and Human Services (HHS) Office for Human Research Protections (OHRP) and our institutional IRB. This project was reviewed by the Ochsner Health Institutional Review Board and was deemed exempt from IRB approval based on institutional guidelines for QI activities. The key criteria met include the following 4 criteria:

1. The intervention (VTE prophylaxis protocol) was developed and implemented solely for the purpose of improving care within Ochsner.

2. The protocol will be implemented at the department level as a clinical standardization initiative, with all patients receiving care under the new protocol as part of routine care.

3. No patient-identifiable data are used in any dissemination of findings. All data are retrospective, deidentified, and securely stored in a HIPAA-compliant system.

4. There are no additional risks or burdens that were imposed on patients outside of standard care practices. A formal determination of exemption was made under internal protocol ID NEU20230216-01, approved by our department leadership on February 16, 2023.

Ethics approval was not required for this protocol per local IRB requirements. However, all authors strictly adhere to patient privacy and confidentiality according to the US HIPAA.

### Outcomes

The primary outcome measure is the rate of VTE. Benchmark data for the primary outcome is derived from ACS NSQIP VTE rates for Ochsner Neurosurgery and the nationwide ACS NSQIP VTE rate. Benchmarks are 2.5% for Ochsner Neurosurgery and 3.27% for the national incidence rate [3]. Secondary outcome measures include the rate of PE, the rate of symptomatic DVT, and the rate of PE-associated mortality.

Process measures have an impact on the primary and secondary outcomes and will include staffing at the time of VTE diagnosis, volume of patients per resident physician, and the percentage of patients at high risk. Balancing measures include the complexity of patients based on VTE risk and history of VTE despite prophylaxis, medication reconciliations, communication with other services, and volume of patients on the neurological ICU. Procedure and patient risk factors of VTE will be included in the analysis as confounding variables. Unintended consequences such as supratherapeutic anticoagulation or bleeding events, delays in mobilization or surgery due to protocol requirements, or variation in adherence will be monitored as well. The mentioned unintended consequences will be monitored through case review and clinical incident reports, and adjustments to the protocol will be made through the Plan-Do-Study-Act cycle framework.

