While the majority of VTEs are asymptomatic, symptomatic VTEs may result in serious adverse events or death [4]. Therefore, prophylaxis of VTE plays a major role in reducing adverse events and unexpected mortality in patients undergoing neurosurgery. An ACS NSQIP data query for Ochsner Department of Neurosurgery performed on August 1, 2022, for the period of July 1, 2020, to June 30, 2021, yielded incidence rates of VTE as follows: a total of 8 events per 320 total neurosurgery cases for a rate of 2.5%, whereas the predicted rate of VTE was calculated to be 2.83% and the expected rate based on the national average rate of VTE was calculated to be 3.27%. This has resulted in an OR calculation of 0.86 (95% CI 0.52-1.42). When stratified by the type of neurosurgery, the VTE incidence rate was 0.76%, where a VTE event occurred in 1 case out of a total of 132 spine neurosurgery cases. The predicted rate for spine neurosurgery was 1.78% and the expected rate for spine neurosurgery cases was 2.24%, with an OR of 0.77 (95% CI 0.37-1.61). The rate of VTE after neurosurgery for brain tumors at Ochsner was 3.52%, based on 5 cases out of 142 total brain tumor neurosurgery cases. The predicted rate of VTE incidence for patients undergoing neurosurgery for brain tumor was 3.45% and its expected rate was 3.42%, with an OR of VTE incidence among patients after brain tumor neurosurgery of 1.01 (95% CI 0.63-1.63).

Although the incidence of VTE at Ochsner Health Department of Neurosurgery is within the expected range of nationwide data [1-3], the lack of a department- or hospital-based protocol for postoperative VTE prophylaxis results in a heterogeneity of patient care and may contribute to unexpected outcomes. Current practice dictates that individual physicians apply their chosen set of VTE prophylaxis guidelines [17]. This further contributes to a heterogeneity of patient care since most guidelines provide inconsistent recommendations (Multimedia Appendix 1). This creates a gap in patient care that could potentially be bridged through a consistent set of department VTE prevention guidelines, which would aim to diminish patient care variability and reduce the incidence of VTE below the national average rates.

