
Continuous improvement is built with small incremental changes, using a systematic scientific approach to test their impact and feasibility. The Plan-Do-Study-Act cycle will be used as a model on which to structure tests of change. This includes continuous analysis of errors and successes of the protocol and subsequent protocol adaptation for the duration of the project. Dynamic data will be assessed through a run chart with data points added monthly, but with interim analysis every 3 months. Interim analyses will be discussed before changing the protocol for such quality improvement adaptations. A formal statistical analysis will be performed with a *t* test comparing NSQIP and postprotocol end-of-study VTE rates at both 12 and 24 months post implementation. Stratification based on malignancy and cranial versus spine procedures will also be assessed, as will be the confounding process and balancing measures.

Missing data will be handled through checking at each interim review. Any record missing critical outcome or key covariate information will be excluded from regression analyses. In addition, we will conduct sensitivity analyses to assess the impact of any missing data on VTE rates. Discrepancies will be resolved by consensus and reported, if indicated. Interim analyses with department reports will be performed every 3 months, but every VTE event will trigger an analysis of the variables described in this protocol. Analyses will consider barriers to change and adequacy of the protocol to guide protocol modifications and continuous implementation of improvements.

Additional guidance has been incorporated to inform future iterations of the protocol, including considerations for patients with comorbid atrial fibrillation or those already on antiplatelet therapy [34]. Implemented changes will be made based on recent evidence in the literature [35].

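### The primary VTE rate depends on how cases are found, yet the plan judges a post-protocol chart-review rate against an NSQIP registry figure, with no guard against a change in detection

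*Protocol article*

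**What the plan says.** Under Methods, Outcomes, "The primary outcome measure is the rate of VTE". No restriction to symptomatic events is attached. Symptoms enter only at the secondary level: "Secondary outcome measures include the rate of PE, the rate of symptomatic DVT, and the rate of PE-associated mortality". Results adds fewer symptomatic PE and DVT events as a secondary success measure. The Introduction (Overview) says: "While the majority of VTEs are asymptomatic, symptomatic VTEs may result in serious adverse events or death".

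Three statements fix the reference rate:
- Outcomes: "Benchmark data for the primary outcome is derived from ACS NSQIP VTE rates for Ochsner Neurosurgery and the nationwide ACS NSQIP VTE rate". The Introduction gives the local figure, "a total of 8 events per 320 total neurosurgery cases for a rate of 2.5" percent, for July 2020 to June 2021.
- Selecting Change plans a formal test "comparing NSQIP and postprotocol end-of-study VTE rates at both 12 and 24 months post implementation".
- Results defines success as at least a 50% reduction from 2.5%, that is, to 1.25% or less.

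Methods (Overview) and another part of Results instead use the 12 months before implementation as the control.

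The project's own data are described as retrospective chart data (Ethical Considerations) and retrospective chart review (Limitations). Selecting Change describes staff training, a displayed flowchart, a monthly run chart and three-monthly department reports, and says that "every VTE event will trigger an analysis of the variables described in this protocol". None of these is described for the control period. The regression covariates named in Results are BMI, malignancy, surgery type and immobility. Limitations names selection bias, performance bias and residual confounding.

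**The concern.** If many VTEs are silent, a rate of all diagnosed VTE mixes two things: how many occur and how many are found. A before-after comparison of such a rate is interpretable only if cases are found in the same way in both periods. Here one stated comparison sets a registry figure against a project chart count. The registry year also ended about 25 months before the adaptation time began on August 1, 2023, so it is not the 12-month control period.

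Training and regular feedback on VTE could plausibly lead staff to test more. The named covariates describe patients and procedures, not how often patients are imaged, so the regression would not remove such a shift. Detection bias is not among the named limitations.

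At stake is a protocol that works but is judged to have missed its target, because the criterion is a fixed rate and more silent events are being found.

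**Working it through.** **1. The plan's own figures.** 8/320 = 0.0250 = 2.5%. Half of that is 1.25%, or 320 × 0.0125 = 4 events. Both reproduce.

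**2. Inputs that must be assumed.** The article says only that most VTEs are asymptomatic. That concerns VTEs that occur, not those that are detected, and no figure is given for either.
- a = silent share of detected events at baseline, taken as 20% to 70%.
- k = detection of silent events after implementation relative to before, taken as 1.5 to 2.
- All symptomatic events are assumed to be found in both periods.

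**3. Formula.** Expected observed events = E × [(1 − a) + a × k], where E is the number expected at unchanged detection. For a true halving, E = 4.

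| a | k | Events | Rate (of 320) |
|---|---|---|---|
| 0.2 | 1.5 | 4 × (0.8 + 0.3) = 4.4 | 1.38% |
| 0.2 | 2 | 4 × (0.8 + 0.4) = 4.8 | 1.50% |
| 0.5 | 1.5 | 4 × (0.5 + 0.75) = 5.0 | 1.56% |
| 0.5 | 2 | 4 × (0.5 + 1.0) = 6.0 | 1.88% |
| 0.7 | 1.5 | 4 × (0.3 + 1.05) = 5.4 | 1.69% |
| 0.7 | 2 | 4 × (0.3 + 1.4) = 6.8 | 2.13% |

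The true 50% reduction would appear as a reduction of 45% (1 − 4.4/8) down to 15% (1 − 6.8/8). The criterion sits exactly at the expected rate for a true halving, so any k above 1 pushes the expected rate past it. To reach 1.25% despite these shifts, the true reduction would have to be 1 − 0.5/1.1 = 55% to 1 − 0.5/1.7 = 71%.

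**4. Cross-check starting from VTEs that occur.** Suppose 30% of occurring VTEs are symptomatic and 10% of silent ones are found at baseline. The true rate is then 2.5%/(0.3 + 0.7 × 0.1) = 6.76%, and the silent share of detected events is 0.07/0.37 = 19%, near the low end used above. If silent detection rises to 25%, a true halving is observed as 0.5 × 6.76% × (0.3 + 0.7 × 0.25) = 1.60%. Hiding the halving completely would need a rise to about 63%.

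**5. The opposite direction.** With no true effect E = 8, and meeting the criterion by detection alone needs 8 × [1 − a(1 − k)] ≤ 4, that is, a(1 − k) ≥ 0.5. At a = 0.2 this is impossible. At a = 0.5 it needs k = 0. At a = 0.7 it needs k ≤ 0.29. Halved silent detection (k = 0.5) gives 7.2, 6.0 and 5.2 events for a = 0.2, 0.5 and 0.7, or 2.25%, 1.88% and 1.63%. All three fail the criterion.

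**The case against.** Four points can be made for the plan.

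**No surveillance scheme is described.** A reader might infer from the event-triggered analysis that patients are actively watched for VTE only after implementation. The text does not support that. The analysis follows a VTE that is already known and finds no silent ones, and no screening is described in either period. This stands: greater awareness is an inference from the training and feedback.

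**Distortion in both directions is not shown.** A reader might infer that a change in detection could just as well produce a false success. That would need a large fall in detection, or lower capture by the chart source than by the registry, and the text shows neither. This also stands. The scenarios with increased detection add 0.4 to 2.8 events to the expected four, so they do not cancel the whole four-event effect.

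**Detected events probably lean symptomatic.** Without screening, the silent share of detected events may be well below the share among all VTEs. That is why the range starts at 20%, where the effect is smaller but the criterion is still missed.

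**The article is condensed and partly covers the point.** Event definitions and queries may sit in a fuller document, the covariate list is open-ended, symptomatic events are collected, and limits on attributing causality are conceded. The absence of those details is not the point here. What remains lies in stated choices: an unrestricted VTE outcome, a formal test against NSQIP, and a success threshold built on the NSQIP figure. Results does use the preceding 12 months for its chi-square or Fisher comparison, but its threshold still starts from 2.5%.

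**Conclusion.** The point holds in a limited form. The primary outcome is sensitive to detection, and the plan both tests and judges it against a rate from a different source and period, without adjusting for detection or naming it as a bias. If awareness raises detection, the likely consequence is a masked benefit: under the assumed ranges, a true halving is observed as about 1.38% to 2.13% instead of 1.25%.

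These are expected values that rest on assumed a and k and ignore chance, which is large in its own right (exact 95% interval for 8/320: 1.09% to 4.87%). The direction of any difference between registry and chart capture cannot be told from the article. The point should be fixed, because the remedy is cheap and the comparison can still be repaired from records. It does not show that the project would wrongly claim success.

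**What to change.** 1. Ascertain VTE in the 12-month control period and the 12-month post period with the same chart query, the same event rule and the same fixed window from surgery. Use that control rate for the primary test and for the 50% reduction criterion. Keep NSQIP as an external benchmark only.
2. Classify each event in both periods as symptom-prompted or incidental. Report symptomatic VTE (symptomatic DVT plus symptomatic PE) as a prespecified sensitivity analysis of the primary result. Requiring it as a co-main result is not necessary, since fewer events would cost precision.
3. Report leg duplex and CT pulmonary angiography studies per 100 patients in each period beside the VTE rate, and name detection bias in Limitations.

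The cost is a small amount of extra chart abstraction: one field per event and two imaging counts per period, with no added imaging. The symptomatic VTE estimate will have a wider interval.

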**Methods:**

This project uses a department-wide protocol of chemical prophylaxis for admitted patients after neurological surgery. This quality improvement (QI) project has been designed and reported in accordance with the SQUIRE 2.0 (Standards for Quality Improvement Reporting Excellence) guidelines. SQUIRE is the most appropriate framework for reporting system-level interventions aimed at improving health care quality, safety, and outcomes. This manuscript addresses all relevant SQUIRE elements. The primary outcome is the VTE incidence over 12 months following protocol implementation. Secondary outcomes include the incidence of pulmonary embolism, length of hospital stay, and unexpected treatment of patients, such as therapeutic anticoagulation, thrombolysis, or emergency surgical or catheter-directed embolectomy. Balancing measures and process measures are also considered. Interim analyses with department reports will be performed every 3 months, but every VTE event will trigger an analysis of the variables described in this protocol. Analyses will consider barriers to change and adequacy of the protocol to guide protocol modifications and continuous implementation of improvements.

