Outcomes of this QI project will be reported to the Ochsner Health Department of Neurosurgery as well as hospital administration. Results will also be shared with the scientific and health care quality improvement community. Consideration of “lessons learned” and suggestions for implementing change in order to improve patient outcomes will be made. In addition, consideration of barriers to change and recommendations for improving patient care will be discussed. This project will provide an evidence base for the implementation of the proposed protocol, and its success or failure to achieve the protocol's aims will be equally important for future hospital patient care quality improvement efforts. Considering there are limited neurosurgical society guidelines on VTE prophylaxis in perioperative patients, results from this project can be used to assess the efficacy of our specific protocol in guiding future guidelines specific for patients undergoing neurosurgery. The overarching objective of this quality improvement initiative is to advance the evidence of the effectiveness of anticoagulation prophylaxis in preventing perioperative VTE morbidity and mortality. As previously identified, the determination of whether implementation of this protocol was a success compared to the current standard-of-care success criteria will be measured against a ≥50% reduction in VTE incidence compared to baseline (from 2.5% to ≤1.25%). Secondary success measures include reduction in symptomatic PE and DVT events, and improvement in protocol adherence across clinical teams.

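### Bleeding is monitored but is not a defined outcome, has no specified pre-post comparison and plays no part in the success criteria, so success on VTE can be declared without a comparative estimate of harm

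*Protocol article*

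**What the plan says.** **Where bleeding appears.** Methods, Outcomes: "Unintended consequences such as supratherapeutic anticoagulation or bleeding events, delays in mobilization or surgery due to protocol requirements, or variation in adherence will be monitored". The next sentence gives the means: "The mentioned unintended consequences will be monitored through case review and clinical incident reports". It adds that the protocol will be adjusted within Plan-Do-Study-Act cycles.

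**Where bleeding does not appear.**
- The primary outcome is the VTE rate.
- Secondary outcomes in Methods, Outcomes: "Secondary outcome measures include the rate of PE, the rate of symptomatic DVT, and the rate of PE-associated mortality".
- Secondary outcomes in the Abstract: "Secondary outcomes include the incidence of pulmonary embolism, length of hospital stay, and unexpected treatment of patients". The examples given of unexpected treatment are all treatments for clots.
- Balancing measures: "Balancing measures include the complexity of patients based on VTE risk and history of VTE despite prophylaxis, medication reconciliations, communication with other services", followed by patient volume on the neurological ICU.
- Process measures: staffing, patients per resident and the share of high-risk patients.
- Success criteria in Results: success "will be measured against a ≥50% reduction in VTE incidence compared to baseline", that is, from 2.5% to at most 1.25%. The secondary success measures are symptomatic PE and DVT and protocol adherence.

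**What is compared.** Methods, Overview defines the previous 12 months as the control for VTE incidence. Results specifies a chi-square or Fisher test on VTE proportions before and after, and a logistic regression with VTE as the dependent variable. The event-triggered analysis in Selecting Change is for VTE events.

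**The concern.** Bleeding is the main expected harm of chemoprophylaxis, and the article itself treats the balance as unsettled. The Introduction reports guidelines that suggest against routine chemoprophylaxis in neurosurgery, and the Discussion describes its safety and utility in spine surgery as controversial. The plan nevertheless gives the benefit a control period, a test, an adjusted model and a success threshold, and gives the harm none of these.

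Methods, Overview relies on assessing outcomes and process measures to keep the project safe, but bleeding is in neither list. If VTE falls to the target, the project reports success, and a reader cannot tell whether bleeding rose, fell or stayed the same. That matters beyond one department, because the Abstract's Conclusions and the Results section say the findings may support guideline recommendations.

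**Working it through.** **1. The plan's own figures.** The Introduction gives 8 VTEs in 320 cases. 8/320 = 2.5%, and half of that is 1.25%. Both agree with the text. The article states no sample size, power, alpha or bleeding rate.

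**2. What the success rule depends on.** Assume 320 cases in the post-period, as in the baseline query. A rate of at most 1.25% means at most 320 × 0.0125 = 4 VTEs. From the binomial distribution:
- P(X ≤ 4 | n = 320, p = 0.025) = 0.10
- P(X ≤ 4 | n = 320, p = 0.0125) = 0.63

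No bleeding term enters the rule, so it does not respond to any bleeding count.

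**3. How much bleeding could change without affecting the decision.** A baseline of 1% to 3% has to be assumed. The extra bleeds from a doubling are 320 × baseline.

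**4. What a pre-post comparison could show.** Assume 320 per period and two-sided alpha 0.05, with p̄ the mean of p1 and p2:

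power = Φ{ [ |p2 − p1| − 1.96·√(2p̄(1 − p̄)/n) ] / √( [p1(1 − p1) + p2(1 − p2)]/n ) }

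For 2% against 4%: p̄ = 0.03, the null standard error is √(2 × 0.03 × 0.97/320) = 0.01349, and the alternative one is √((0.0196 + 0.0384)/320) = 0.01346. Power = Φ[(0.02 − 0.02643)/0.01346] = Φ(−0.478) = 0.32.

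Size per period for 80% power: n = [1.96·√(2p̄(1 − p̄)) + 0.842·√(p1(1 − p1) + p2(1 − p2))]² / (p2 − p1)².

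| Assumed baseline | Doubled | Extra bleeds per 320 | Power, 320 per period | n per period for 80% |
|---|---|---|---|---|
| 1% | 2% | 3.2 | 18% | 2319 |
| 1.5% | 3% | 4.8 | 25% | 1534 |
| 2% | 4% | 6.4 | 32% | 1141 |
| 3% | 6% | 9.6 | 45% | 749 |

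**5. Why capture must be the same in both periods.** If the baseline b were fully captured and only half of the post-period bleeds were, a true doubling would appear as 2b × 0.5 = b, which is no change. The 50% is illustrative. The document says nothing about completeness of capture.

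**The case against.** **Bleeding is not ignored.** The article names it, and case review is an active route alongside incident reports. There is a stated response through Plan-Do-Study-Act cycles, with interim review every 3 months. The balancing measures are introduced as examples and need not be a closed list. All of this stands. A reader might infer that bleeding is caught only through spontaneous reports, but the text does not support that. Reviewing and reacting to individual cases still produces no rate and no comparison.

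**The pre-post wording could cover bleeding.** Results speaks generally of comparing outcomes across the two 12-month periods, and Ethical Considerations describes the data as retrospective. A reader might infer that bleeding is collected only after implementation, but the document does not say so. What can be said is that no pre-period bleeding rate or comparison is specified, and that bleeding is not among the listed outcomes to which the general wording would apply.

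**An article condenses.** The bleeding definition, time window and extraction fields may sit in a fuller document, and their absence here is not the point. The point rests on the outcome lists, the named control and test, and the success rule, all of which the article states.

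**Exposure may not have increased.** A reader might infer that chemoprophylaxis becomes wider and higher-dose than before. That comes from setting the Selecting Change steps against the physician-chosen care described in the Introduction. Earlier use and doses are not quantified, so it remains an inference.

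**The exemption statement.** Ethical Considerations says: "There are no additional risks or burdens that were imposed on patients outside of standard care practices". This is a criterion for exemption from review, not a result the project sets out to test. It cannot be called wrong on these documents, though the plan specifies no comparison that could check it.

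**The comparison would be imprecise.** This is true, as the table shows. It argues for an estimate with an interval in place of a test, not for having no estimate.

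**Conclusion.** The point holds in this form: bleeding is monitored, but it is not a primary, secondary or listed balancing outcome, has no specified pre-post comparison and is absent from the success criteria. Success can therefore be declared on VTE with no comparative estimate of bleeding.

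The size rests on assumptions, because the article gives no bleeding rate. With 320 cases per period (the July 2020 to June 2021 count carried forward) and a 1% to 3% baseline, a doubling is about 3 to 10 additional bleeds per 320 patients and leaves the success decision unchanged. A reader might go further and set these against the 4 VTEs the target would prevent (8 − 4 per 320), as if one bleed cancelled one VTE. The documents give no basis for that weighting, and nothing in them shows that bleeding will rise. This is a weakness in what the project can conclude. It should be corrected, but it does not invalidate the VTE comparison.

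**What to change.** 1. In Methods, Outcomes, make postoperative bleeding a named balancing outcome with one definition and one time window chosen by the clinical team.
2. Extract it from charts in the same way in both 12-month periods. Case review, incident reports and Plan-Do-Study-Act adjustment can continue alongside for individual events.
3. Report the pre-post difference in bleeding rate with a 95% CI beside the VTE result, as an estimate and not as a significance test.
4. In Results, state that the VTE success criterion is read jointly with the bleeding estimate.

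**Cost.** Some added chart fields in both periods. The planned pre-post logistic regression already needs patient-level data from both, which limits the extra work. It would be larger if the baseline were taken only from NSQIP rates, as parts of the article suggest. The estimate will be imprecise: at an assumed 2% in both periods, the 95% half-width is 1.96 × √(2 × 0.02 × 0.98/320) = 2.2 percentage points. No dose or clinical rule needs to change for this.
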